**Design:**

This is a three-arm cluster-randomized controlled superiority trial (cRCT). The study arms include the following: group 1: NIPP; group 2: NIPP+, and group 3: control. Groups 1 and 2 will receive a 12-week intervention (NIPP or NIPP+) with active monitoring and longitudinal follow-up at 2, 6, and 12 months post-intervention. Additionally, an in-depth process and performance evaluation of each intervention arm will be undertaken using quantitative and qualitative methods. A total of 60 clusters from 5 subcounties of the Agago district will be randomly selected, and 15 households per cluster will be recruited using specific inclusion/exclusion criteria for a total of 900 households (300/arm). Respondents for the qualitative portion will be purposely selected.

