## Study overview, design, and setting

This is a three-arm cluster-randomized controlled superiority study (cRCT) with a 1:1:1 allocation ratio. The study arms will be group 1: NIPP arm, group 2: NIPP+ arm, and group 3: control arm. Each intervention arm will receive a 12-week intervention (NIPP or NIPP+) with active monitoring and longitudinal follow-ups post-intervention.

The study will be conducted in the Agago District of Northern Uganda in communities in which the subjects live and work. Agago District is an example of a complex environment in that households and communities there are recovering from conflict and are also likely to suffer from frequent droughts, livestock and human disease, and other hazards. Subcounties included in the study are detailed in Table 1. Exclusion criteria for subcounties were as follows:
Areas with similar behavioral changed interventions like Community Conversation (CC) and Community Led Total SanitationUrban or semi-urban areasHigh levels of food insecurityAreas of current and previous nutritional interventions

**Table 1 Tab1:** List of subcounties from Agago District, Uganda, and maximum number of clusters possible per subcounty

Subcounty^a^	Number of parishes	Number of households in subcounty (estimated)	Max number of clusters^b^ in any one subcounty
Omot	4	1342	12
Lokole	7	2398	21
Omiya Pachwa	6	3226	18
Patongo	6	3239	18
Arum	8	3993	24
Kuywee	5	2874	15
Parabongo	7	2015	21
Lira-Palwo	3	2070	9
Paimol	4	2172	12
Agengo	6	2791	18

^a^Subcounties were excluded based upon being a locale with similar behavioral change interventions, containing an urban or semi-urban area, having high levels of food insecurity, or being included in current and previous nutritional interventions

^b^A cluster will be a group of 3 NIPP (or NIPP+) circles whether be the women’s, men’s, or community circles and be made of one or more “villages” because of the small population size in some of the parishes of Agago

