### Sample size calculation and sampling strategy

To detect meaningful differences in the change in the primary outcome measures across the three arms with a power of 0.80, a significance level of 0.05, and an intra-class correlation of 0.05, each treatment arm will require 17 clusters with 15 households (with children under the age of 2) in each cluster (Table 2). We used secondary data on all outcome measures (except total coliform) from Northern Uganda and collected as part of the Feed the Future Innovation Lab for Nutrition Uganda Birth Cohort Study [24]. We aim to follow the same households throughout the duration of the study. Thus, the sample size is adjusted for 20% attrition. This increase will come from additional clusters and not households (to keep the integrity of the NIPP 15 households/circle programmatic design). The sample will include 20 clusters per arm for a total of 60 clusters and 15 households per cluster with an overall household sample size of 900. Based on the results of cluster randomization, trained study personnel will approach households that meet the study’s inclusion criteria in the parishes selected for the study. They will approach eligible households and seek consent until a total of 15 households agree thus forming a cluster. The sampling at the household level is purposeful. A random subsample of households will be taken at 2 months and interviewed again at 6 months post-intervention. This sample size is a fixed sample of 82 households per intervention arm.

**Table 2 Tab2:** Sample size calculation for quantitative evaluation

Category	Mean	*SD*	ICC^a^	Effect size (Cohn’s)	Sample size/treatment arm	Total sample size
*E. coli*	31.56	45.14	0.05	0.67	120 (20 clusters*5 hh per cluster + 20% for attrition)	≈ 360
Aflatoxin	20	43.6	0.05	0.34	306 (17 clusters*15 hh per cluster + 20% for attrition)	≈ 900

^a^The ICC calculated for aflatoxin for mothers was close to 0 but came from a small sample size. Thus, we have decided to overestimate the ICC to 0.05

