The criteria for community selection include food security, water access, security, community cohesion, and geographic proximity to one another to decrease the probability of contamination between the arms (GOAL 2018). These criteria will be applied in the selection of all 60 clusters (intervention and control). Tufts will utilize block randomization to randomly assign clusters to 1 of 3 treatment groups and will only share the list of clusters by treatment arm (not how they were assigned). A total of 60 clusters (a “cluster” is a group of 3 NIPP circles and may be at either parish or village level, dependent on population density — see Table 1 for subcounty-level estimates of cluster representation) will be randomly assigned to the three groups (20 clusters per group). We will randomize at the parish level by assigning random numbers to each parish, ranking the parishes by random assignment, and assigning to a treatment group after the ranking is complete such that group 1 is randomized to Control, group 2 to NIPP, and group 3 to NIPP+. The households will be selected purposefully after clusters have been randomized to specific arms. Each cluster in groups 1 and 2 will have one male, one female, and one community NIPP circle. Each circle will include 10–15 individuals with the cluster serving as the primary unit of analysis. As this is a community-based intervention cluster-randomized trial, it is impossible to conceal from participants which treatment arm they have been randomized to and which intervention they have the opportunity to consent to being a part of.

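### The allocation paragraph names two units of randomisation, cluster and parish; the stated sample size holds only if clusters were randomised individually

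*Protocol article*

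**What the plan says.** The section on sample size and sampling strategy gives two allocation procedures in one paragraph.

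- Cluster: "Tufts will utilize block randomization to randomly assign clusters to 1 of 3 treatment groups". The paragraph then puts 60 clusters into three groups of 20.
- Parish: "We will randomize at the parish level by assigning random numbers to each parish, ranking the parishes by random assignment", with arms assigned once the ranking is done.

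A cluster is a group of three circles that "may be at either parish or village level, dependent on population density". The same paragraph makes the cluster the primary unit of analysis. The sample size also counts clusters: "each treatment arm will require 17 clusters with 15 households (with children under the age of 2) in each cluster", with a single ICC of 0.05, raised to 20 clusters per arm for attrition.

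The number of subcounties is given in two ways. The abstract says: "A total of 60 clusters from 5 subcounties of the Agago district will be randomly selected". The section on study overview, design and setting says: "Subcounties included in the study are detailed in Table 1", and that table has ten rows.

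The arms are also numbered in two ways. The abstract and the design section have group 1 as NIPP, group 2 as NIPP+ and group 3 as control. The allocation paragraph has "group 1 is randomized to Control, group 2 to NIPP, and group 3 to NIPP" (the last of these being NIPP+), followed by "Each cluster in groups 1 and 2 will have one male, one female, and one community NIPP circle".

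**The concern.** In a cluster-randomised trial, the unit that was allocated fixes the design effect and the degrees of freedom for every between-arm comparison. If parishes were allocated and a parish holds two or three clusters, those clusters share one allocation and are not independent replicates of the arm. A calculation that counts 20 clusters per arm then overstates the information. An analysis clustered only on the 15-household group leaves out any variance shared across a parish, which makes confidence intervals too narrow. The text as written does not let an analyst tell which situation applies.

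**Working it through.** **Inputs from the article.** Power 0.80, significance level 0.05 (taken as two-sided; the article does not say), ICC 0.05, 15 households per cluster, 17 clusters per arm required and 20 planned, 20% attrition, effect sizes 0.34 (aflatoxin) and 0.67 (*E. coli*). Table 1 gives the number of parishes and the maximum number of clusters per subcounty.

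**Step 1: the plan's own figure.** A two-sample comparison at 0.34 needs 136 per arm. The design effect is 1 + 14 × 0.05 = 1.70, so 136 × 1.70 = 231.2 households, or 231.2 / 15 = 15.4 clusters. With a t-based calculation on 2(k − 1) degrees of freedom, power is 0.789 at k = 16 and 0.815 at k = 17. The stated 17 is therefore reproduced, with each cluster as an independently allocated unit. With 20 such clusters and 12 households left in each, power is 0.83.

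**Step 2: parish counts.** Table 1 gives 4 + 7 + 6 + 6 + 8 + 5 + 7 + 3 + 4 + 6 = 56 parishes. The maximum number of clusters is three times the number of parishes in every row (168 in total). The five largest subcounties hold 8 + 7 + 7 + 6 + 6 = 34 parishes and the five smallest hold 3 + 4 + 4 + 5 + 6 = 22. Since 56 is less than 60, some parishes must hold more than one cluster even if all ten subcounties are used. With five subcounties there are 22/3 ≈ 7 to 34/3 ≈ 11 parishes per arm.

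**Step 3: power if parishes are allocated.** Let m be households per cluster, c the clusters per parish (60 / parishes, spread evenly) and ρ the correlation between households in different clusters of one parish. The article gives no ρ, so 0 to 0.05 is an assumed range.

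Design effect = 1 + (m − 1) × 0.05 + (c − 1) × m × ρ, with t-based power on 2 × (parishes per arm − 1) degrees of freedom.

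Example: 34 parishes, m = 12, ρ = 0.05. Then c = 60/34 = 1.76 and the design effect is 1.55 + 0.765 × 12 × 0.05 = 2.009. The effective size is 240 / 2.009 = 119.5 per arm, which gives power 0.71.

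Aflatoxin power:

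| Parishes | Households per arm | ρ = 0 | 0.01 | 0.025 | 0.05 |
|---|---|---|---|---|---|
| 34 | 300 | 0.86 | 0.84 | 0.80 | 0.75 |
| 34 | 240 (20% loss) | 0.81 | 0.79 | 0.76 | 0.71 |
| 22 | 300 | 0.84 | 0.78 | 0.71 | 0.60 |
| 22 | 240 (20% loss) | 0.79 | 0.74 | 0.67 | 0.57 |
| 56 | 240 (20% loss) | 0.83 | 0.83 | 0.82 | 0.82 |

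For *E. coli* (0.67, 5 households per cluster, 34 parishes), power is 0.98 at ρ = 0 and 0.97 at ρ = 0.05.

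**Step 4: type I error if only the cluster is modelled.** At m = 15 this is 2 × [1 − Φ(1.96 / √(DE / 1.70))], where DE is the Step 3 design effect. At ρ = 0 it is 5%.

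- 34 parishes: 7.0% at ρ = 0.025 (DE 1.987) and 9.0% at 0.05 (DE 2.274).
- 22 parishes: 9.5% at 0.025 (DE 2.348) and 14.0% at 0.05 (DE 2.995).
- 56 parishes: 5.4% at 0.05 (DE 1.754).

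**The case against.** A reader might infer that parishes were in fact randomised, so that the 80% power and the standard errors are simply wrong. The documents do not support that.

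- The same paragraph also has the 60 clusters themselves assigned, and the sample-size paragraph refers to the results of cluster randomisation. On that reading the 17 clusters stand.
- If all ten subcounties of Table 1 are used and clusters are spread over the 56 parishes, the loss is negligible (0.82 against 0.83 after attrition).
- The parish correlation is an assumption. The footnote to Table 2 says the aflatoxin ICC for mothers was near zero in a small sample and that 0.05 is deliberately high. The upper end of the range makes households in different clusters of a parish as alike as households in one cluster. With 34 parishes and full enrolment, power stays at 0.80 up to a correlation of about 0.025.
- The statistical methods section promises to control for the complex survey design in all analyses, and this could include the parish. Random-effect levels and degrees-of-freedom corrections are commonly left to the analysis plan, so their absence is not held against the article.

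All of this stands, and it makes the consequences conditional. It does not remove the contradiction: an analysis plan cannot recover the unit of randomisation from a text that states it in two ways.

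A reader might also infer from the renumbered arms that control would receive circles and NIPP+ none. The article consistently describes control as receiving no intervention, so this is a labelling conflict and no more.

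**Conclusion.** The article contradicts itself on the unit of randomisation, and this needs correcting. The sample size and the cluster as unit of analysis are sound if clusters were allocated individually.

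If the parish step was followed within five subcounties, there are about 7 to 11 randomised units per arm instead of 20. Aflatoxin power after 20% loss could then be anywhere from 0.81 to 0.57, and an analysis clustered only on the 15-household group could have a type I error of up to 9% (34 parishes) or 14% (22 parishes). With 22 parishes, power after loss is just under 0.80 even at zero parish correlation, through lost degrees of freedom alone. *E. coli* power is little affected with 34 parishes.

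These sizes rest on an assumed parish correlation of 0 to 0.05, an even spread of clusters over all parishes in the chosen subcounties, and a two-sided 5% test. The parish counts and the conflict of wording rest on no assumption.

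**What to change.** - State the one unit that was actually randomised, and how many of these units are in each arm.
- Reconcile the five subcounties of the abstract with the ten in Table 1.
- If the unit was the parish, account for clustering at that level, with a parish random effect above cluster and household or with parish-level robust errors, and with small-sample degrees of freedom in either case. Restate power with the actual number of parishes per arm and a stated parish-level ICC.
- If the unit was the cluster, delete the sentence on ranking parishes.
- Refer to the arms by name in the allocation paragraph and the allocation list, and reconcile the group numbers with the rest of the article.

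The cost is wording and, if parishes were allocated, a model term and possibly a less favourable stated power. No new clusters or data are needed.

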### Inclusion/exclusion criteria

In groups 1 and 2, within each cluster, community leaders will be approached to identify literate individuals with specific practices that are recommended by the NIPP approach. These individuals will be invited to become NIPP volunteers. The inclusion criteria for the NIPP volunteers are as follows: willingness to implement the interventions in the circles over a 12-week period, have a healthy child age less than 24 months, and are approved by community leaders. The inclusion criteria for the NIPP female circle participants are as follows: willingness to participate in the group, are planning to stay in the area for 12 weeks, and have a child under the age of 2 (irrespective of nutritional status). The inclusion criteria for the NIPP male circle participants are as follows: willingness to participate, are planning to stay in the area for 12 weeks, and are a spouse, brother, and/or other influential male family members of the female caregiver enrolled in the female circle. There were no specific criteria for the community circle other than being key community leaders. Age is not a direct criterion either for the NIPP volunteers or for the NIPP circle participants though we specifically note that the participant must be a caregiver of a child under the age of 2. In the context of Uganda that caregiver could be a grandmother, adoptive parent, or older sibling, hence, there was no age cut-off. Exclusion criteria for both the NIPP and NIPP+ interventions are as follows: no child under age 2 in the household or not being present in the selected communities during the intervention and data collection periods and/or not willing to participate through the entire 12-week cycle. People can refuse to participate in the interview but continue to participate in the program. There are no specific criteria for default/dropout in the NIPP approach. However, volunteers will visit households where participants have missed 3 consecutive visits to inquire about their participant status. Participants who voluntarily exit the NIPP or NIPP+ program will still be surveyed but may voluntarily decline to participate in the interview at each time point. However, volunteers will visit households where participants have missed a session to inquire about their participant status. If a participant has missed 2 consecutive sessions and cannot be traced or voluntarily exit, they are considered as a defaulter.

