#### Statistical methods for assessing impact

For the analysis, we will use an intent-to-treat (ITT) approach using the initial randomization of the treatment arms. While we know that there could be some contamination across groups or non-adherence, we will plan for the clusters to be sufficiently far apart that this should limit any bias related to self-selection captured via retention or adherence. Using ITT will allow us to determine the overall impact of having the NIPP vs. NIPP+ vs. control in your community, thus better mimicking real-world program implementation and impact. Each survey question will have the option of “Refused to Answer” or “Don’t Know” and will eventually be transformed into missing variables. Prior to that transformation, we will use the proportion of RA or DK responses to understand the sensitivity of the question itself. We will use the standard rule where if fewer than 5% of your observations are missing, the variable will remain in the analysis. If the 5% or more of observations are missing, we will not use the variable to avoid drawing inaccurate inferences. We will not impute missing data.

For the analysis, we will take advantage of the panel to run mixed effects models, allowing us to determine the role of time-variant and invariant individual household, and community characteristics, as well as measures of exposure and integration on key outcome indicators (Table 1 above). In addition, we will use a difference-in-difference analysis (baseline/endline, baseline/sustainability, endline/sustainability) to triangulate findings. To complement these models, the analysis will also leverage exploratory analysis to identify cross-cutting or underlying correlations using principal component analysis. For all of the analysis, we will control for a host of individual-, household-, and community-level characteristics.

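### Households are chosen after cluster allocation with the arm known, so recruitment can make the arms differ, chiefly against control and chiefly for aflatoxin

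*Protocol article*

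**What the plan says.** The section on sample size and sampling strategy fixes both the order and the method of recruitment. Allocation comes first: "Based on the results of cluster randomization, trained study personnel will approach households". Selection is not random: "The sampling at the household level is purposeful", and again "The households will be selected purposefully after clusters have been randomized to specific arms". It stops at a quota: "They will approach eligible households and seek consent until a total of 15 households agree thus forming a cluster". The randomising institution "will only share the list of clusters by treatment arm (not how they were assigned"), so the method of assignment is withheld but the arm is not. On households, the article states that "it is impossible to conceal from participants which treatment arm they have been randomized to", and it adds that they know which intervention they are consenting to.

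The section on inclusion and exclusion criteria lists willingness to take part and planning to stay 12 weeks for members of the female and male circles. It introduces the exclusions with "Exclusion criteria for both the NIPP and NIPP+ interventions are as follows"; one of them is unwillingness to complete the 12-week cycle. Control has no circles and no cycle. For control households the article gives only the general requirement of a child under 2 and a reference to the study's inclusion criteria.

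The section on statistical methods plans intent-to-treat, mixed models, difference-in-difference and covariate-adjusted models. It mentions self-selection only through retention or adherence, and its remedy is distance between clusters. It also claims: "Using ITT will allow us to determine the overall impact of having the NIPP vs. NIPP+ vs. control in your community".

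**The concern.** Cluster randomisation balances the clusters, in expectation. It balances the households only if they are fixed before allocation, or recruited afterwards in a way that cannot depend on the arm. Here staff choose purposefully with the allocation in hand. In the intervention arms a household accepts circle meetings two to three times a week, while in control it accepts surveys and samples only. If the households who accept these different offers also differ in diet, water handling or grain storage, part of the observed contrast reflects who was enrolled and not what the programme did.

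Intent-to-treat keeps each household in the arm in which it was recruited, so it preserves such a difference. Distance between clusters limits contamination but has no bearing on who enrols. The sample also consists of purposefully chosen, consenting households, which is narrower than the community-level impact claimed.

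**Working it through.** **1. The plan's own figure.** Inputs from the sample size section and Table 2: aflatoxin effect 0.34 SD, power 0.80, significance level 0.05 (two-sided assumed), ICC 0.05, 15 households per cluster.

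- Per arm, ignoring clustering: 2 × (1.960 + 0.842)² / 0.34² = 135.8, so 136.
- Design effect: 1 + (15 − 1) × 0.05 = 1.70.
- 136 × 1.70 = 231.2 households, or 231.2 / 15 = 15.4 clusters. Adding one cluster as the usual small-sample correction gives 16.4, so 17.
- Check with a noncentral t on 2(k − 1) degrees of freedom: power is 0.789 at k = 16 and 0.815 at k = 17.
- 17 × 15 = 255, and 255 × 1.2 = 306, as printed.

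The 17 clusters per arm reproduce. The point concerns recruitment, not sample size.

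**2. Which contrasts are exposed.**

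| Route | NIPP or NIPP+ vs control | NIPP vs NIPP+ |
|---|---|---|
| Willingness and stay criteria written only for circle participants | yes | no, same criteria in both |
| Purposeful approach by staff acting on the allocation | yes | yes |
| Consent given knowing the arm | yes | yes |

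**3. Which outcomes can be corrected (Table 3).** Dietary diversity, *E. coli* and food security are measured at baseline, so baseline differencing can remove a fixed level difference; a difference in trend would remain. Aflatoxin is listed at endline and sustainability only, and the data collection section places maize sampling a few months after each of those points. Of the three planned difference-in-difference contrasts, the two that start from baseline are therefore unavailable for aflatoxin. The endline-to-sustainability contrast cannot recover an effect already present at endline.

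**4. Illustration of size.** The shifts below are assumptions; the documents give none.

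- 20 clusters × 15: SE = √(2 × 1.70 / 300) = 0.106 SD.
- 20 clusters × 12 (20% of households lost): design effect 1 + 11 × 0.05 = 1.55, SE = √(2 × 1.55 / 240) = 0.114 SD.
- With no true effect and a recruitment shift b, the two-sided rejection rate is 1 − Φ(1.96 − b/SE) + Φ(−1.96 − b/SE).

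| Assumed shift b (SD) | In Table 2 aflatoxin units (SD 43.6) | Error rate, 20 × 15 | Error rate, 20 × 12 |
|---|---|---|---|
| 0.05 | 2.2 | 7.6% | 7.3% |
| 0.10 | 4.4 | 15.6% | 14% |
| 0.15 | 6.5 | 29% | 26% |
| 0.20 | 8.7 | 47% | 42% |

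The calculation shows sensitivity to a shift in either direction. It does not show that a shift exists.

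**The case against.** - **No imbalance is shown.** A reader might infer that the arms will differ by self-selection. The text does not support that; it shows a route, not a result. This objection stands.
- **The criteria may be meant for all arms.** Recruitment in the selected parishes refers to the study's inclusion criteria, control households must also consent and are to be followed throughout, and a condensed article may leave a control list to the full protocol. This lowers confidence in the asymmetry. It does not remove the point: as written, the criteria concern circles and a cycle that control lacks, and purposeful selection after allocation is stated outright for all arms.
- **NIPP versus NIPP+ is a central contrast, and both arms share the same criteria.** This stands, and the conclusion is limited accordingly.
- **Adjustment is already planned.** Difference-in-difference and covariate models are in the plan and help for outcomes with a baseline. It would be wrong to say that diets and water must look better in the intervention arms without any effect. For aflatoxin only covariate adjustment is left, and that can correct only for what was measured.
- **The size cannot be derived.** One might assume 60% of households willing and a 0.3 SD gap between willing and unwilling households, giving (1 − 0.6) × 0.3 = 0.12 SD, or 0.12 / 0.34 = 35% of the planned aflatoxin effect. Neither input is in the documents, the formula treats control as unselected although control households also consent, and the direction is open because households with poorer practices might be keener to join. That figure should not be relied on.

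**Conclusion.** The concern holds in a limited form. The plan builds in a route to recruitment bias after randomisation: selection is purposeful and arm-aware, consent is given knowing the arm, and the participation criteria are written only for the intervention circles. Comparisons of NIPP or NIPP+ with control are most exposed, and among outcomes aflatoxin, which has no baseline and sets the 900-household sample. NIPP versus NIPP+ is exposed only through approach and consent.

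Neither the direction nor the size of any bias is known. Under the plan's ICC of 0.05, 20 clusters of 15 per arm and a normal approximation, an assumed shift of 0.10 SD, less than a third of the planned 0.34 SD, would take the false-positive rate from 5% to about 16%. The order and method of selection are stated clearly. Whether the circle criteria were also meant for control is less certain.

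The claim about community-level impact is a separate matter of scope. It does not fit a purposeful sample of consenting households, but it is not evidence of a difference between arms.

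**What to change.** **Clusters not yet recruited.** Apply one eligibility set in all three arms: a child under 2, plans to stay, and willing to take part if offered. Complete household selection, consent and baseline in a cluster before its arm is disclosed to recruiters and households. Where a list of eligible households exists, draw the 15 at random or approach them in random order. The plan already draws its water-sample households at random, although only from those enrolled.

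**Clusters already recruited** (the trial status section gives March 2021 as the start). Report numbers approached, eligible and refusing by arm, and compare baseline characteristics by arm. State the recruitment-bias limitation for aflatoxin against control, and limit the claim to enrolled households. The covariate adjustment already planned should stay, but it is not a new safeguard.

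**Cost.** Changing the order of fieldwork is cheap. A full listing may not be: Table 1 sums to 26,120 households over 168 possible clusters, about 155 per cluster, so 60 clusters could mean about 9,300 households if each cluster covers its whole area. That is why random selection is suggested only where a list is available. Some households may withdraw once the arm is disclosed. They should still be surveyed in their assigned arm, as the article already intends for those who leave the programme. Refusals matter, because the plan does not impute and drops variables with 5% or more missing.
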